| Title:        | Adaptation and assessment of a common element treatment approach designed to improve mental health in forcibly displaced individuals.                                                                                                                                                                                                                                                                                                                                                                                                                                                                                                                                                                                                                                                                                                                                                                                                                                                                                                                                                                                                                                                      |
| Population:   | 
Venezuelan migrants living in Lima (Peru), n = 90 (n = 60 in the intervention and n = 30 in waitlist control), of male and female biological sex, 18 years old or older, with depression (<math>\leq 10</math> in PHQ9), anxiety (<math>\leq 10</math> in GAD7) and/or post-traumatic stress disorder (history of trauma exposure, LEC 5 and <math>\leq 31</math> in PCL 5). Participants with suicidality, homicidality or psychosis will be excluded.
 
Lay-providers n = 10, of male and female biological sex, 18 years old or older, of any nationality.
                                                                                                                                                                                                                                                                                                                                                                                                                                                                                                                                                                                                                  |

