|                                        | will be identified and trained as supervisors. Following the training, these supervisors lead small practice groups and supervision groups, closely supported and supervised by psychologists. We will engage a total of $n = 10$ providers, each of which will engage with $n = 9$ participants ( $n = 6$ pilot, $n = 3$ waitlist control).                                                                                                                                                                                                                                                                                                                                                                                                                                                                                                                                                                                                                                                                                                                                                                                                                                                                                                                                  |

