## 4.2 Study Outcome Measures

### 4.2.1 Primary Outcome Measures

Since the intervention is transdiagnostic and addresses several CMD, there will be three primary outcome measures. Changes in anxiety will be measured using the GAD7 scale. This is a 7-item instrument that measures generalized anxiety. Changes in depression will be assessed using the PHQ9 questionnaire, which is a 9-item instrument that measures depression. Both instruments have been chosen because they are short, easy to administer and have been widely used in research. Spanish versions of GAD7 and PHQ9 have been validated and used in Venezuelan and Peruvian populations. Furthermore, prior studies with this same population conducted by the main researcher have used these instruments. Regarding PTSD, changes will be measured using the PCL5 checklist which has been validated for its use in Spanish-speaking populations and utilized in research projects with similar populations. The LEC5, which identifies potentially traumatic events in the life course of the participants, will be used at baseline and in the follow-up assessments along with the PCL5.

The primary outcomes will be measured at baseline during screening and at endline 12 weeks after baseline in the case of waitlist control. In the intervention group, they will be assessed at baseline during screening, weekly (PCL5) or every two weeks (PHQ9 and GAD7) throughout the intervention before the next session, after the last session of the intervention and at 1-, 3-, and 6-month follow-ups after completion of the intervention. Participants will be sent a secure REDCap link, where they will be asked to answer each item of the instruments.

See appendix with the English and Spanish versions of the instruments.

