### 15.3 Statistical Methods

All analyses will be performed using multiple packages within SPSS and R. Descriptive statistics will be calculated with frequencies and percentages or means and standard deviations. Demographic variables will be tested for differences in distribution with bi-variate analyses. Variable distributions will be examined, and transformations made, when distributions are skewed or otherwise violate parametric analytic assumptions. All reasons for missing data will be tabulated by reason and reported. All quantitative outcomes will be tested at two-sided  $\alpha=.05$  level. Regression analysis will examine changes in primary outcomes in depression, anxiety and post-traumatic stress disorder symptoms and feasibility and acceptability in recruitment rate, assessment completion rate, attendance rate and acceptability rated by providers and participants. Regression will plot the trends in outcome variables over the three study periods (baseline, post-intervention and 6 months following). We will also explore the relationship between covariates and baseline outcome scores and retention, fidelity, and satisfaction to identify any characteristics that might be associated with implementation success. All analyses will adjust for sex as a covariate and it will be tested as an effect modifier (e.g. stratification).

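### Section 15.3 names sex, but not the baseline score of each scale, as a covariate in the efficacy regression on change, which can waste precision

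*Protocol*

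**What the plan says.** Section 15.3 sets the form of the efficacy analysis: "Regression analysis will examine changes in primary outcomes in depression, anxiety and post-traumatic stress disorder symptoms". It adds "Regression will plot the trends in outcome variables over the three study periods (baseline, post-intervention and 6 months following"), and it names a covariate for everything: "All analyses will adjust for sex as a covariate and it will be tested as an effect modifier (e.g. stratification").

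The only place in 15.3 where baseline scores appear as something to relate to another variable is exploratory and concerns implementation: "We will also explore the relationship between covariates and baseline outcome scores and retention, fidelity, and satisfaction".

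The baseline scores exist in both arms. Section 4.2.1 says of the control arm: "The primary outcomes will be measured at baseline during screening and at endline 12 weeks after baseline in the case of waitlist control". Of the other arm it says: "In the intervention group, they will be assessed at baseline during screening". The table in section 12 places this assessment before enrolment and randomisation. The planned size is "n = 90 (n = 60 in the intervention and n = 30 in waitlist control").

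**The concern.** The baseline value of a symptom scale is usually among the best predictors of its later value. Here it is measured in everyone before allocation, so adjusting for it is legitimate and free. Section 15.3 nevertheless gives an outcome form (change) and a covariate for all analyses (sex) and does not list the baseline score beside it.

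Subtracting the baseline fixes its coefficient at one. ANCOVA estimates the coefficient from the data. Unless the true coefficient happens to be one, the change score has the larger variance, and a chance difference between arms at baseline passes partly into the estimate. With only 30 controls, and no stratification by severity described in section 5, such differences will be common. At stake is the width of the interval for each of three primary outcomes in a small trial.

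**Working it through.** **The plan's own figure.** Section 15.2 gives n = 59 to detect a problem that affects 5% of participants. At an assumed 95% confidence, ln(0.05)/ln(0.95) = 58.40, which rounds up to 59. The figure reproduces, but it concerns problem detection and says nothing about the precision of the arm comparison.

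**Which time points carry the randomised contrast.** The waitlist arm has a baseline and one endline at 12 weeks and is then treated (section 4.2.1; section 2, Design/Methodology). By the 6-month assessment there is no untreated control. The arm comparison therefore uses two time points. With two time points and complete data, an arm-by-time term with unconstrained baseline means equals the difference in mean change.

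**Inputs.** From the protocol: 60 and 30 participants, two-sided alpha 0.05. Assumed, because the protocol does not give them: correlation r between baseline and endline of 0.3 to 0.7; ratio k of baseline SD to endline SD of 1 or 0.7; no dropout.

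**Variance factors, endline SD set to 1.**
- Change score: Vc = 1 + k² − 2rk
- ANCOVA: Va = 1 − r²
- Difference: Vc − Va = (k − r)², so the saving is (k − r)²/(1 + k² − 2rk). It cannot be negative and is zero only when k = r.

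| r | k | Vc | Va | saving |
|---|---|---|---|---|
| 0.3 | 1 | 1.40 | 0.91 | 35% |
| 0.5 | 1 | 1.00 | 0.75 | 25% |
| 0.7 | 1 | 0.60 | 0.51 | 15% |
| 0.3 | 0.7 | 1.07 | 0.91 | 15% |
| 0.5 | 0.7 | 0.79 | 0.75 | 5% |
| 0.7 | 0.7 | 0.51 | 0.51 | 0% |

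**In terms of detectable difference.** The allocation factor is sqrt(1/60 + 1/30) = 0.2236. At 80% power the detectable difference is (1.960 + 0.842) × 0.2236 × sqrt(V) = 0.626 × sqrt(V), in endline SDs.
- k = 1: from 0.74 to 0.60, 0.63 to 0.54, and 0.49 to 0.45 at r = 0.3, 0.5, 0.7. A change-score analysis would need 90 × 2/(1 + r), about 138, 120 or 106 participants, to match ANCOVA with 90.
- k = 0.7: from 0.65 to 0.60, 0.56 to 0.54, and 0.45 to 0.45.

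**Simulation check (k = 1, true difference 0.5 SD, 4,000 runs per r, sex in both models).** Empirical standard errors, change score against ANCOVA, were 0.266/0.214, 0.228/0.201 and 0.174/0.161. The squared ratios are 0.65, 0.77 and 0.86, against 0.65, 0.75 and 0.85 from the formula. Power was 0.45/0.62, 0.59/0.71 and 0.80/0.86. Both estimators averaged close to 0.5 in size, so neither is biased.

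**Chance imbalance.** The baseline difference between arms has a standard error of 0.2236 baseline SDs. A difference above 0.25 in either direction has z = 0.25/0.2236 = 1.118, a probability of about 26% for each scale. Given such an imbalance, the change-score estimate shifts by (k − r) × 0.25: by 0.175, 0.125 or 0.075 endline SDs at k = 1, and by 0.10, 0.05 or 0 at k = 0.7.

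**The case against.** **The text does not say sex only, or that baseline is unused.** A reader might infer both. Neither is supported. Section 15.3 does not exclude other covariates, and baseline is part of the change and one of the three periods in the trend. What can be said is narrower: sex is the covariate named for all analyses, and the baseline score is not named as one in the efficacy model.

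**A change score as dependent variable is not certain.** The reference to changes may be loose wording, and the trend sentence suggests a longitudinal model. Such a model with a common baseline mean would have about the precision of ANCOVA. This stands in part: the loss depends on how the model is built. But no such constraint is stated, and without it the two-time-point contrast reduces to a difference in change.

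**The detail may belong in a statistical analysis plan.** One may exist and is not shown. If the protocol were silent, there would be no point to raise. It is not silent: it gives an outcome form and a covariate for every analysis, and that stated choice can be improved.

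**The size of the gain is uncertain.** This stands. The 15% to 35% range needs equal SDs at both times. Participants enter by scoring at or above a cut-off on at least one scale (section 7.1), which can compress baseline SDs, and the gain may then be close to nothing.

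**Providers.** From "We will engage a total of $n = 10$ providers, each of which will engage with $n = 9$ participants" a reader might infer that the model wrongly treats participants as independent. The protocol does not say so. Any inflation would rest on an assumed intraclass correlation, and a random effect on ten providers is a debatable choice usually left to the analysis plan. It forms no part of this point.

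**Conclusion.** The point holds as one of efficiency. Section 15.3 describes regression on change with sex as the named covariate, and naming the baseline value of each scale would be a better specification. In large samples it cannot lose precision against the change score. With 90 participants, if k happened to equal r, it would cost no more than roughly the one degree of freedom. The variance saving runs from 35% down to 15% for r of 0.3 to 0.7 with equal SDs, and from about 15% down to 0% if the baseline SD is 0.7 of the endline SD. Both r and the SDs are assumptions.

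A reader might go further and call the planned comparison biased or invalid. It is neither: under randomisation both estimators are unbiased, and the imbalance shift above is conditional on an imbalance having occurred. For a pilot sized for problem detection this is a worthwhile, inexpensive clarification and not a threat to validity.

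**What to change.** Add one sentence to section 15.3: for the between-arm comparison, each primary outcome at endline is regressed on arm, the baseline value of the same scale, and sex. If the longitudinal model is kept for that comparison, state instead that baseline means are constrained to be equal across arms. The descriptive trends over the three periods can stay as they are.

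The cost is one degree of freedom per model and no new data. The sentence relies on the protocol's definition of endline. Section 12 counts endline from the first session, or within 14 days of completion, in the intervention arm and from baseline in the waitlist arm. Adding the covariate does not settle that difference.

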## 16 Ethics/Protection of Human Subjects

This study is to be conducted according to applicable US federal regulations and institutional policies (which are based in federal regulations, guidance, and ICH Good Clinical Practice guidelines).

This protocol and any amendments will be submitted to the Boston Medical Center and Boston University Medical Campus IRB / Universidad del Pacífico for formal approval of the study conduct. The decision of the IRB concerning the conduct of the study will be made in writing to the investigator. A copy of the initial IRB approval letter will be provided to the sponsor, the National Institute of Mental Health, before commencement of this study.

All subjects for this study will be provided a consent form describing this study and providing sufficient information for subjects to make an informed decision about their participation in this study. The consent form will be submitted with the protocol for review and approval by the IRB. The consent of a subject, using the IRB-approved consent form, must be obtained before that subject is submitted to any study procedure. Consent will be documented as required by the IRB.

